**Figure 1 Fig1:**
[figure not shown]
CONSORT diagram. ERP, exposure and response prevention; MB-ERP, mindfulness-based exposure and response prevention; NHS, National Health Service; OCD, obsessive compulsive disorder.

#### Mindfulness-based exposure and response groups

The MB-ERP group will be provided with 10 sessions of mindfulness-based behaviour therapy (ERP), each session lasting two hours. Session 1 will introduce the rationale for ERP alongside the rationale for including mindfulness principles and practice. Sessions 2 to 9 will each start with a 10-minute mindfulness practice: mindfulness of the breath and body (session 1); mindfulness of the breath, body, sounds and thoughts (sessions 2-3); mindfulness of thoughts (session 4-5); and mindfulness of body, thoughts, urges and action (sessions 6-10). Mindfulness practice will be followed by a 20-minute Socratic inquiry about the practices in order to draw out learning, with a particular emphasis on the three areas noted above: non-judgmental acceptance of (intrusive) thoughts, non-judgmental acceptance of physical sensations (of anxiety) and a recognition that it is possible to choose whether or not to follow behavioural urges (to engage in compulsive behaviours). A three-minute mindfulness breathing space practice [12] will also be introduced from session 6 onwards for participants to use on a daily basis to bring awareness to current experiences and to facilitate engagement in ERP tasks. In session 1, participants will be given an MP3 player with the range of mindfulness practices for daily home practice, with practice being recorded in the daily diary. The final 90 minutes of MB-ERP session will follow the same ERP protocol outlined above with the addition that whilst engaging in ERP tasks, participants will be encouraged to bring mindfulness skills to the tasks. In particular, this will involve an encouragement to bring mindfulness to intrusive thoughts as they arise (allowing thoughts to arise without suppressing them or becoming absorbed with them), to bring mindfulness to physical sensations of anxiety (noticing and accepting physical sensations of anxiety with curiosity and interest) and to bring mindfulness to urges to engage in compulsive behaviours (noticing compulsive urges and recognising there is a choice available - a choice to follow the urge and a choice to allow the urge to remain, without following it). Session 10 will focus on consolidating learning from the therapy and developing a therapy blueprint for continuing MB-ERP after the therapy has concluded. As with the standard ERP groups, therapy sessions will be audio recorded and rated by an expert to monitor and ensure therapy fidelity. This expert will provide regular supervision to the group facilitators. Additional supervision will be provided by an expert MBI therapist in order to ensure adherence to MBI principles and practice.

### Data analysis

Participant characteristics will be examined at baseline to check that the randomisation procedure has been successful and any differences between the two treatment groups are at a minimum. This will include a check of between-group differences on demographic variables (age and gender) and on all the outcome measures by examining the descriptive statistics. The primary outcomes will be evaluated through an intention-to-treat analysis using linear mixed models to allow for missing data that is assumed to be missing at random. For each primary outcome, treatment effects will be calculated simultaneously at both the post-therapy and the six-month follow-up time points after adjusting for the outcome measure at baseline and site. The models will include treatment group (ERP or MB-ERP), time (post-therapy or six-months follow-up) a time-treatment interaction and a random intercept. Corresponding standard errors, significance levels and 95% confidence intervals will be calculated for all treatment effects.

Data from the Change Interview will be analysed using Thematic Analysis [36] within each condition (that is, a separate thematic analysis for the ERP and MB-ERP conditions). This will elucidate participants’ subjective experiences of change in each type of intervention and participants’ views on mechanisms of change, which the Change Interview specifically addresses.

For the full trial, effect sizes alongside the minimum clinically important difference, where relevant, on the primary outcomes (Y-BOCS-II and engagement) will be used to conduct a sample size calculation. Recruitment rates to the study will be presented in terms of ‘number of participants consented to the study per research assistant days - that is, how many research assistant days are taken on average in order to consent one participant. This will allow us to estimate the research assistant time that will be needed for recruitment in a full trial, once the sample size calculation is conducted. Data completeness will be monitored, and the percentage of consenting participants contributing to all data-collection points will be reported. If completeness falls below 95%, the research team will consider strategies for improving future data collection and handling missing data. Similarly, if once recruited, the retention rate falls below 80%, the research team will explore methods to increase retention in the full trial. Data quality will be overseen by the trial statistician.

Between-group effect sizes and data from the Change Interview will inform a funding application for a definitive trial of MB-ERP. If effect sizes on the primary outcome measures (Y-BOCS-II, number of therapy sessions attended and number of between-session ERP tasks completed) are in favour of MB-ERP in comparison to ERP, funding for a definitive trial will be sought, which may include modifications to the current therapy and study design depending on findings from the quantitative data analysis, review of recruitment and retention rates, and from the Change Interview. If effect sizes on the primary outcome measures are not in favour of MB-ERP in comparison to ERP, the research team will review possible reasons for this, drawing on the Change Interview findings and this will inform the next stage in this programme of research.

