A group of six people, all with lived experience of OCD who had experience of ERP and mindfulness-based approaches, were consulted when developing this protocol. The group advised that an integrated mindfulness-based ERP group would be more likely to improve symptom outcomes and to enhance engagement in comparison to either type of intervention (that is, MBI or ERP) on its own. In light of this advice and the background literature outlined above, we expect that a mindfulness-based approach to group ERP would be more effective and have lower rates of drop-out than group ERP on its own.

Given the lack of research in this area to date [21], this is a protocol for a pilot randomised controlled trial (RCT). The research question for the definitive trial is as follows: ‘Is group mindfulness-based ERP more effective at reducing OCD symptom severity and better at enhancing therapy engagement than standard group ERP for people diagnosed with OCD?’ The primary aim of this pilot study is to estimate the size and direction of the treatment effect, and the corresponding 95% confidence interval, by comparing mindfulness-based ERP (MB-ERP) groups to standard exposure and response prevention (ERP) groups on the primary outcome measures of OCD symptom severity and therapy engagement. If the magnitude of these effects are deemed clinically relevant, then the estimate will be used in a power calculation for the definitive trial. Secondary aims of the definitive study will be to test effects on other important outcome (depression and wellbeing) and process (mindfulness and obsessive-compulsive beliefs) measures and so these measures are included in the pilot study to assess their feasibility. In addition, the pilot study will gather information on rates of recruitment and will record rates of attrition from the study. A semi-structured interview with participants will also be conducted to ascertain experiences of change and attributions for change from participants’ perspectives. Information from these interviews will inform the development of future research in this area.

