## Methods/Design

### Design and sample size

This is a pilot study for a single blind, prospective RCT using an intention-to-treat comparison of two treatment groups (MB-ERP and ERP). Measures will be taken at baseline (Time 1), post-therapy (Time 2) and at 6 months post-therapy (Time 3). A power calculation to determine sample size is not appropriate for this pilot study [23,24], as there is no intention to identify a statistically significant difference between the two treatment groups. This study follows recommendations for pilot RCTs [25] and aims to have at least 12 participants per treatment arm who provide full data. We aim to recruit 40 people with OCD to allow up to 40% attrition from the study, which is a conservative estimate of what might be expected to occur in ERP [8].

This study has received full ethical approval through the South East Coast (Surrey) arm of the National Research Ethics System in the UK (Research Ethics Committee reference: 13/LO/1768).

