### Procedure

Figure 1 shows the flow of participants through the pilot RCT. Patients with a diagnosis of OCD will be sought through mental health teams in the host NHS trust. Informed consent will be obtained from each participant. Potential participants will be given a copy of the study participant information sheet and will have the opportunity to discuss the study in person with the research assistant (RA) before signing the consent form. The study research assistant will conduct the baseline assessments of consenting participants on the above measures within four weeks of the groups starting. After baseline assessments have been completed, participants will be randomly allocated to either an MB-ERP or an ERP group by a Clinical Trials Unit using block randomisation. Ten participants will be allocated to each group so that there will be two MB-ERP groups and two ERP groups in total. Ten therapy sessions for each group will be facilitated by two clinical psychologists, at least one of whom will be an accredited Cognitive Behavioural Therapy (CBT) therapist and an accredited mindfulness-based cognitive therapy teacher. Sessions will be held either in NHS premises or suitable community venues. Post-group assessments on each of the outcome measures will be conducted by a second RA who will be blind to group allocation.

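### The analysis model has no therapy-group level although both therapies are delivered in four groups of ten, so the primary 95% confidence interval will be too narrow if outcomes correlate within groups

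*Protocol article*

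**What the plan says.** Under Procedure, individuals are randomised but treated in groups. Allocation is individual ("participants will be randomly allocated to either an MB-ERP or an ERP group by a Clinical Trials Unit using block randomisation"), and delivery is in four groups: "Ten participants will be allocated to each group so that there will be two MB-ERP groups and two ERP groups in total". Each group has its own course of sessions: "Ten therapy sessions for each group will be facilitated by two clinical psychologists".

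Under Data analysis, the primary outcomes are analysed by linear mixed models adjusted for the baseline value and site. The remaining terms are listed: "The models will include treatment group (ERP or MB-ERP), time (post-therapy or six-months follow-up) a time-treatment interaction and a random intercept". The level of the random intercept is not named. No therapy-group term, ICC or other allowance for clustering appears there or elsewhere in the article.

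Under Background, the primary aim is to "estimate the size and direction of the treatment effect, and the corresponding 95% confidence interval". The estimate then feeds the power calculation for a definitive trial, whose question again concerns group delivery.

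**The concern.** People treated in the same therapy group share facilitators, sessions and group process. Their outcomes, including attendance and between-session task completion, may therefore be more alike than those of people in different groups of the same arm. The article fixes its model by listing the terms, and none of them represents this.

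A single intercept cannot serve two levels. With two follow-up times per person, the natural reading is a participant intercept, which leaves therapy group out. If it meant therapy group instead, the repeated measures on each person would be unmodelled.

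The site term does not fill the gap. Each therapy group belongs to one arm, so site can absorb at most what both arms share at a site. Variation between groups within an arm stays in the treatment contrast.

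At stake is the honesty of the interval that the pilot exists to produce, together with the significance levels reported beside it.

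**Working it through.** **Inputs from the article.** Four therapy groups, two per arm, ten participants each (Procedure). Recruitment of 40 with up to 40% attrition, and at least 12 per arm with full data (Design and sample size). A 95% interval (Background).

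**Assumed input.** The ICC of the outcome within therapy groups. The article gives none, so 0 to 0.10 is used as the main range.

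**The plan's own figure.** 2 × 12 = 24 completers; 24 / (1 − 0.40) = 40. The recruitment target reproduces. After 40% attrition each group has on average 10 × 0.60 = 6 members analysed.

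**Formulas.** With m analysed per group:
- design effect DE = 1 + (m − 1) × ICC
- ratio of true to independence standard error = √DE
- approximate coverage of the nominal 95% interval = 2Φ(1.96/√DE) − 1

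| m | ICC | DE | √DE | Coverage |
|---|---|---|---|---|
| 10 | 0 | 1.00 | 1.00 | 95% |
| 10 | 0.02 | 1.18 | 1.09 | 93% |
| 10 | 0.05 | 1.45 | 1.20 | 90% |
| 10 | 0.10 | 1.90 | 1.38 | 84% |
| 6 | 0.02 | 1.10 | 1.05 | 94% |
| 6 | 0.05 | 1.25 | 1.12 | 92% |
| 6 | 0.10 | 1.50 | 1.22 | 89% |

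Worked example, m = 10 and ICC 0.05: DE = 1 + 9 × 0.05 = 1.45; √1.45 = 1.20; 1.96/1.20 = 1.63; coverage 90%.

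**Simulation check.** A simulation of 200,000 replicates at one time point, without covariates, gave 95.0% at ICC 0. At ICC 0.01, 0.05 and 0.10 it gave 94.0%, 89.6% and 84.0% for m = 10, and 94.5%, 92.0% and 88.6% for m = 6. The problem is negligible at 0.01 and material from about 0.05.

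A second simulation added baseline adjustment and a site term. It assumed two sites with one group per arm at each, a layout the article does not state. Without attrition, coverage was 92.1%, 89.4% and 84.2% at ICC 0.02, 0.05 and 0.10. The site term brings no improvement.

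**What four groups can support.** An analysis with therapy group as the unit has 4 − 2 = 2 degrees of freedom, with t = 4.30. It restored 95% coverage in simulation, but the expected half-width is much larger. For m = 10 and ICC 0.05 it is 4.30 × √(2 × 1.45/20) = 4.30 × 0.381 = 1.64 SD, against about 0.63 SD from the unclustered analysis. For m = 6 the figures are 1.96 and 0.84 SD. The data cannot both estimate the group variance and give a usefully narrow interval.

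**Consequence for a later trial with groups of ten.** At ICC 0.02 to 0.10, DE is 1.18 to 1.90, so 18% to 90% more participants are needed than a calculation without the design effect would give.

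**The case against.** The strongest objection is that the size of the problem is entirely assumed. At ICC 0 the stated interval is correct, and at ICC 0.02 with six per group its coverage is about 94%. This stands: the article does not establish that the interval is too narrow, only that it will be if the ICC is above zero.

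Second, no decision depends on the interval's width. The article says "A power calculation to determine sample size is not appropriate for this pilot study", and its go-ahead rule uses the direction of the effect sizes, which ignoring clustering does not bias. This also stands and lowers the severity, but the interval remains part of the stated primary aim.

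Third, random-effects detail is commonly left to an analysis plan, which is not shown. This carries less weight here, because the article lists the model terms down to site. For sessions attended, a single count per person, the argument that one intercept cannot serve two levels does not apply. An intercept there could be the therapy group, although it would rest on only four groups.

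Fourth, some circumstances that would sharpen the point are not stated. The article does not say that groups are closed to new members, does not define site (it names one host trust), and does not say whether facilitator pairs differ between groups. If one pair ran both arms, additive therapist effects would cancel in the contrast, though group-process effects would remain.

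A reader might infer that the definitive trial will be planned without a design effect and so be too small. No section says so: the article says only that effect sizes and, where relevant, the minimum clinically important difference will be used, and that the design may be modified. Nor would such a trial be 18% to 90% too small. Those figures are the extra participants needed; the shortfall would be 1 − 1/1.18 = 15% to 1 − 1/1.90 = 47% of the required number.

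**Conclusion.** The point holds in conditional form. For the repeated outcomes, on the natural reading of the model, clustering by therapy group is ignored. The nominal 95% interval then covers about 93%, 90% and 84% with ten analysed per group, and about 94%, 92% and 89% with six, at assumed ICCs of 0.02, 0.05 and 0.10. These figures rest on the assumed ICCs, equal group sizes and the same ICC in both arms.

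It does not follow that the treatment estimate is biased, or that 40 is the wrong number. The target is not based on power, and it reproduces from the article's own attrition allowance. This should be fixed, but it does not undermine the pilot.

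**What to change.** In Data analysis:

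1. Name the random intercept as participant level for the repeated outcomes. State that therapy group is a further source of correlation which four groups (2 degrees of freedom) are too few to estimate reliably.
2. Alongside the model-based interval, report sensitivity intervals with the treatment-effect standard error multiplied by √(1 + (m − 1) × ICC), where m is the mean number analysed per group. Use a prespecified range such as ICC 0, 0.02, 0.05 and 0.10. No single value should be the headline, because the article gives no basis for choosing one.
3. State that these intervals depend on the assumed ICC, and that the pilot's precision is limited by having two groups per arm.
4. State that the definitive trial's sample size will include a design effect for group delivery.

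The cost is a few lines of text. Over ICC 0.02 to 0.10 the sensitivity intervals are about 5% (m = 6, ICC 0.02) to 38% (m = 10, ICC 0.10) wider than the model-based one. No new data or participants are needed. The multiplier restores coverage only if the assumed ICC is about right, which is why a range is needed.

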### Participants

Participants will be 40 adults referred to a mental health trust in the South of the England. Inclusion criteria are that participants (1) meet DSM-IV [26] diagnostic criteria for OCD; (2) have been stable on psychiatric medication for at least 3 months prior to the consent meeting; (3) have no plans for changes to psychiatric medication during the course of the study; (4) have not received psychological therapy in the past three months or have any plans for psychological therapy during the course of the study; and (5) are older than 18 18 years of age. Exclusion criteria are as follows: those who have an identified organic cause for their OCD symptoms, a diagnosed learning disability, or if they meet the diagnostic criteria, based on the Mini International Neuropsychiatric Interview (MINI version 6.0.0) [27], for a psychotic disorder, post-traumatic stress disorder, anorexia nervosa, alcohol abuse or substance abuse (non-alcohol). This will be ascertained through the care team. To reflect the reality of mental health services and the comorbidity of OCD with other mental health conditions [2], comorbidity will not be an exclusion criterion. People presenting with hoarding-only compulsions will be excluded from the study, given the recent move to classify hoarding as distinct from OCD [1].

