### Measures

#### Diagnostic status

*Mini International Neuropsychiatric Interview* (*MINI version 6.0.0*) [27]. DSM-IV OCD diagnostic criteria [26] will be established at all three time points using the Mini International Neuropsychiatric Interview. Meeting diagnostic criteria at baseline is an inclusion criterion for the study.

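### The recruitment rate is counted per consent, but projecting research-assistant time for the full trial calls for a rate per randomised participant

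*Protocol article*

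**What the plan says.** The Background section lists recruitment rates among the things the pilot will record. The Data analysis section fixes the unit, "how many research assistant days are taken on average in order to consent one participant", and states its use: it will let the team "estimate the research assistant time that will be needed for recruitment in a full trial, once the sample size calculation is conducted".

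The Procedure section gives the order of events. Informed consent is taken, and then "The study research assistant will conduct the baseline assessments of consenting participants on the above measures within four weeks of the groups starting". Allocation follows: "After baseline assessments have been completed, participants will be randomly allocated to either an MB-ERP or an ERP group".

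Under Diagnostic status, the OCD criteria "will be established at all three time points using the Mini International Neuropsychiatric Interview", and "Meeting diagnostic criteria at baseline is an inclusion criterion for the study".

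Two statements bear on how many consenters could be lost. The Procedure section says "Patients with a diagnosis of OCD will be sought through mental health teams in the host NHS trust". The Participants section, after listing the exclusions, says "This will be ascertained through the care team".

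**The concern.** The sample size of the full trial will come from effect sizes on the primary outcomes, so it will count people in a randomised comparison. The recruitment rate counts people who have signed a consent form. Between these two events stands an interview that can find a person ineligible, and there is also time in which a person can withdraw. Anyone lost there lowers the reported days per recruit without adding to the randomised sample.

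The pilot exists to set parameters for a definitive trial, and this is one of them. If the rate is applied directly to a number to randomise, the staffing request for the full trial will be right or too low, never too high.

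**Working it through.** **Inputs from the protocol article**

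- Unit of the rate: research-assistant days per consent (Data analysis). Call it d.
- Use of the rate: full-trial recruitment time, once the sample size is known (Data analysis). The article names no multiplier.
- Order: consent, then baseline with the diagnostic interview, then randomisation (Procedure; Diagnostic status).
- Pilot target: at least 12 per arm with full data, up to 40% attrition, 40 recruited (Design and sample size).
- Allocation: ten people to each of two MB-ERP and two ERP groups (Procedure).

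**Inputs that are assumed**

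- f, the share of consenters never randomised. The article gives none, so a range from 0 to 30% is shown.
- N = 200 to randomise in the full trial, for illustration only.

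**Step 1: the plan's own figure.** 2 × 12 = 24 with full data, and 24 / (1 − 0.40) = 40. This matches the stated 40. The number allocated is 4 × 10 = 40 as well. The pilot's own target is therefore a number of people allocated, with no allowance for consenters who do not reach allocation.

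**Step 2: the projection.** To randomise N people, N / (1 − f) must consent.

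- Days needed: d × N / (1 − f)
- Days projected if d is applied to N directly: d × N
- Shortfall as a share of the true need: 1 − (1 − f) = f
- Extra days relative to the projection: 1 / (1 − f) − 1 = f / (1 − f)

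| f (assumed) | Consents needed for N = 200 | Shortfall against true need | Extra days over projection |
|---|---|---|---|
| 0 | 200 | 0% | 0% |
| 5% | 211 | 5% | 5.3% |
| 10% | 223 | 10% | 11.1% |
| 20% | 250 | 20% | 25% |
| 30% | 286 | 30% | 42.9% |

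The last two columns describe the same gap on different bases. Since f cannot be negative, the gap is never in the other direction.

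**Step 3: could another planned figure close the gap?** The Data analysis section will also report the percentage of consenting participants who contribute at every data-collection point. Suppose 200 people with complete data are wanted, 90% of consenters are randomised and 80% of those randomised complete (all assumed). Then 200 / 0.8 = 250 must be randomised and 200 / (0.9 × 0.8) = 278 must consent. Days per consent multiplied by 278 is correct, whereas multiplied by 250 it is about 10% short. So a conversion through the consent-based percentage would remove the shortfall.

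**The case against.** The strongest reply is that the article never writes the multiplication. It says only that the rate will allow an estimate once the sample size is known, and days per consent is a sound descriptive figure in itself. This stands: the mismatch lies between the unit and its declared use, and a shortfall arises only if the rate is applied to a number to randomise.

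The second reply is that the completeness percentage has the same denominator as the rate and would convert a sample size into a number to consent, as Step 3 shows. The arithmetic is right, but the plan does not propose that conversion. It uses the percentage to prompt better data collection and handling of missing data. The percentage also mixes loss before randomisation with missing data up to six months after therapy, so f cannot be read from it. Inflating by it would count anyone with one missing assessment as lost, although the planned mixed model keeps partial data.

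Third, f may be small. Referrals already carry a diagnosis, and the care team is the source for exclusions, although the article does not say whether that check precedes consent. This stands too, and it limits the likely size. It is not a reason to leave f unreported, since the protocol itself rechecks the diagnosis at baseline.

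A reader might also infer that the metric is faulty because it contains no calendar time and cannot show whether groups of ten can be filled within the four-week baseline window. The article does not support that as an error. The metric's stated purpose is staff time, and the four-week limit applies to baseline assessment rather than to consent, so consenters can be accumulated beforehand.

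**Conclusion.** The point holds as a small improvement to a feasibility metric. The unit does not match its stated use, and any resulting error is favourable: a shortfall of f against the true need, or f / (1 − f) more days than projected. This rests on two conditions: that some consenters are not randomised, and that the rate is applied to a number to randomise.

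A reader might conclude that the plan does understate research-assistant time, by 11% to 43%. The article does not support that. It documents no loss between consent and randomisation, the percentages follow from assumed values of f, and f may be near zero. Those figures are also extra days over the projection; measured against the true need, the corresponding shortfalls are 10% to 30%.

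The pilot's target of 40, its effect estimates and confidence intervals are unaffected. So is the decision to seek funding, which turns on effect sizes; recruitment is reviewed only for possible changes to the design.

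**What to change.** In the Data analysis section, report research-assistant days per randomised participant, together with the per-consent figure and the proportion of consenters who are randomised. State that the per-randomised figure will be used for the full-trial estimate.

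The change is to wording. It needs only the numbers consented and randomised, which a participant-flow record would ordinarily hold, and the same count of research-assistant days. The one drawback is that the reported recruitment figure may look slightly less favourable. Counts per calendar month and the time from consent to the first session could be added if the team finds them useful, but they are optional and not part of the correction.
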